**Trial registration number:**

ISRCTN14332621; pre-results.

Strengths and limitations of this studyFirst large-scale randomised controlled clinical trial comparing chlorhexidine 0.2% to natamycin 5% for the treatment of fungal keratitis.This study benefits from a pragmatic design: as a non-inferiority trial, if chlorhexidine is found to be within a predefined non-inferiority margin of 0.15 logMAR of natamycin at 3 months a recommendation to use chlorhexidine 0.2% can be made; this is a far cheaper, easy to formulate medication that could significantly increase access to antifungal treatment for the target population.Clinicians are masked to the treatment allocation, however, due to different physical appearance it is not possible to mask patients to their allocated treatment.This study will also assess the superiority of either medication as well as a number of key secondary outcome measures, analysed by arm.First randomised controlled trial investigating fungal keratitis to use in vivo confocal microscopy as a diagnostic tool for the detection of fungal elements.

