### Outcome assessments

Participants will be reassessed at 2 days, 1 week, 2 weeks, 3 weeks, 2 months and 3 months following enrolment. Additional examinations, outside the trial protocol schedule may be conducted by the supervising clinician as indicated. The specific assessments to be carried out at each visit are indicated in table 3. These will be conducted in the same way described for the baseline assessment as described (table 2). At each follow-up assessment, the participant will be asked about adherence to treatment and symptoms, including side effects, if still receiving trial treatment. This will be recorded in the case record file. To monitor trial medication adherence, the study participants will be asked to bring their eye-drop bottles to the 1-week, 2-week and 3-week follow-ups. The amount of remaining medication will be measured by weighing the bottle and will be compared with the anticipated remaining amount provided the drops were being used as instructed, resulting in a ratio of actually remaining to what is anticipated. Participants will be resupplied with medication as needed. The presenting visual acuity will be measured on each visit. In addition, the BSCVA will also be measured at the 3-month follow-up (primary outcome measure). At the final 3-month follow-up, the three quality of life questionnaires will be repeated. On each occasion the eyes will be examined using a slit-lamp and the cornea photographed. The IVCM will be repeated at 1, 2 and 3 weeks to determine whether there is evidence of fungal hyphae resolution with the fragmentation of linear elements. At the 1-week follow-up if the ulcer has not healed it will be rescraped for repeat culture to determine whether the keratitis is now culture positive or culture negative. We will give the study participants appointment cards for the next follow-up and they will be reminded about the follow-up a week prior to the date. Public transport costs will be paid for participants who are outpatients.

**Table 3 T3:** Baseline and follow-up assessment components

Assessment item	Baseline	Day 2	Day 7	Day 14	Day 21	Day 60	Day 90
History/baseline questionnaire	X						
Check treatment adherence		X	X	X	X	X	X
Check for side effects		X	X	X	X	X	X
Visual acuity—presenting	X	X	X	X	X	X	X
Visual acuity—BSCVA	X						X
Contrast sensitivity	X						X
Slit-lamp examination	X	X	X	X	X	X	X
Cornea photography	X	X	X	X	X	X	X
In vivo confocal microscopy	X		X	X	X		
Cornea samples (microbiology/PCR)	X		X				

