	For HRQoL, we will use the EQ-5D questionnaire, EQ-Visual Analogue Scale and the WHOQOL-BREF. The EQ-5D is a standardised tool to measure health outcomes.^38^ The WHOQOL-BREF has good applicability in (LMIC as it was developed simultaneously from concept across 18 countries in Africa, Asia and Latin America. It measures four domains of health: Physical Health, Psychological Health, Social Relationships, and Environment. Details of this scoring are given in table 2.^39^
	Analysis will be by comparing the scores obtained for each QoL assessment for the two treatment arms to estimate the effect of CHX and NATA on patients’ QoL. This will be similar to that performed by Habtamu *et al*.^40^ Comparisons between the two medication groups will be adjusted for the matching variables: age and sex. The VRQoL analysis was also adjusted for socio-economic status and the HRQoL analysis adjusted for both socioeconomic status and presence of health problems during the previous 4 weeks, as these factors may confound the association between fungal keratitis and QoL. Logistic, linear and ordinal logistic regression methods will be used for binary, continuous and ordered categorical outcome variable analysis, respectively. Linear regression models and the t-test were employed to compare significant differences in QoL scores and to generate mean and mean differences between the two treatment arms in each QoL subscale and domain, respectively.
Cost-effectiveness analysis, using EQ-5D data from 3 months and direct cost data	Direct cost data will be collected at the 3 months follow-up. Economic costs to the patient can also be calculated from the EQ-5D questionnaire, which will be asked at baseline and at the 3 months follow-up. Mean direct costs incurred by patients will be compared between interventional arms using the t-test for significance. The difference from the baseline EQ-5D and the 3 months EQ-5D mean scores will also be compared in a similar fashion.
Drug adherence	The rate of drug adherence will be compared between the two treatment groups using descriptive statistics.

BSCVA, best spectacle corrected visual acuity; EQ-5D, EuroQol-5 dimensions; LMIC, low-income and middle-income countries; QoL, quality of life; TPK, therapeutic penetrating keratoplasty.

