## Ethics and dissemination

Ethics committee and regulatory review and approval has been obtained from the Nepal Health Research Council (NHRC) Ethics Committee, Kathmandu, Nepal; the Department of Drug Administration (DDA), Kathmandu, Nepal; and the London School of Hygiene and Tropical Medicine Ethics Committee, UK. The trial is registered with the ISRCTN clinical trials registry. Protocol modifications are submitted to the relevant parties for review and/or approval. Table 5 summarises the study protocol and trial registration information. At the end of the study period, patients who still require treatment or follow-up will continue to be treated at SCEH as per routine clinical practice. The trial sponsor is the LSHTM. The results of this trial will be presented at local and international meetings and submitted to peer-reviewed journals for publication.

**Table 5 T5:** Registration data and protocol summary

Data category	Information
Primary registry and trial identifying no	ISRCTN Registry; ISRCTN14332621
Date of registration in primary registry	15 May 2019
Secondary identifying numbers	
Source(s) of monetary or material support	Wellcome Trust
Primary sponsor	London School of Hygiene and Tropical Medicine
Secondary sponsor(s)	
Contact for queries	[name] FRCOphth ([contact])
Title	Chlorhexidine 0.2% vs Natamycin 5% for the treatment of fungal corneal infections
Countries of recruitment	Nepal
Health condition(s) or problem(s) studied	Fungal keratitis
Intervention(s)	Participants will be randomised to either topical chlorhexidine 0.2% or topical natamycin 5%
Key eligibility criteria	1. Acute MK characterised by:
	Corneal epithelial ulceration >1 mm diameter
	Corneal stromal infiltrate
	Acute inflammation: for example, conjunctival injection, anterior chamber inflammatory cells, hypopyon
	2. Filamentous fungal hyphae visualised on smear microscopy and/or in vivo confocal microscopy
	3. Agree to be randomised to either treatment arm and able to give informed consent
	4. Agree to be followed up at 2 days, 1 week, 2 weeks, 3 weeks, 2 months and 3 months
	5. Adults (18 years and older)
Study type	Randomised controlled trial
Date of first enrolment	1 June 2019
Target sample size	500
Recruitment status	Recruiting
Primary outcome(s)	Best Spectacle Corrected Visual Acuity at 3 months by a trial certified optometrist
Key secondary outcomes	1. Time to full epithelial healing (slit lamp examination by ophthalmic clinician)

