	2. Pin-hole visual acuity in logMAR at 3 months, trial-certified optometrist
	3. Scar/infiltrate size at 1 week, 3 weeks and 3 months (slit-lamp examination by ophthalmic clinician)
	4. Ulcer depth at 1 week and 3 weeks (slit-lamp examination by ophthalmic clinician).
	5. Hypopyon height at 1 and 3 weeks, (slit-lamp examination by ophthalmic clinician).
	6. Perforation and/or TPK by 3 months (slit-lamp examination by ophthalmic clinician).
	7. Positive culture rate at 1 week
	8. Ocular adverse effects at each follow-up visit (day 2, day 7, day 14, 3 weeks, 2 months, 3 months), slit-lamp examination by ophthalmic clinician
	9. Quality of life (QoL) assessed using: EQ-5D, WHO/PBD-VF20, WHOQOL-BREF (comparison between baseline and QoL measures at 3 months)
	10. Cost-effectiveness analysis, using EQ-5D data from 3 months and direct cost data
	11. Drug adherence at each follow-up visit (day 2, day 7, day 14, 3 weeks, 2 months, 3 months) while the patient is using study medications

EQ-5D, EuroQol-5 Dimension; LMIC, low-income and middle-income countries; MK, microbial keratitis; TPK, therapeutic penetrating keratoplasty.

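### The outcome named as a cost-effectiveness analysis is planned as two separate comparisons of cost and EQ-5D change, so as written it gives no cost-effectiveness estimate

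*Protocol article*

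**What the plan says.** Table 5 of the protocol article, captioned "Registration data and protocol summary", gives as item 10 of its key secondary outcomes: "Cost-effectiveness analysis, using EQ-5D data from 3 months and direct cost data". Table 4 carries a row under the same name and is presented as the place where the analysis of each secondary outcome is set out.

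That row states two analyses:

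- **Cost:** "Mean direct costs incurred by patients will be compared between interventional arms using the t-test for significance".
- **Effect:** "The difference from the baseline EQ-5D and the 3 months EQ-5D mean scores will also be compared in a similar fashion".

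On data, the row says "Direct cost data will be collected at the 3 months follow-up". It adds that "Economic costs to the patient can also be calculated from the EQ-5D questionnaire", although Table 2 describes the EQ-5D as a measure of health outcomes. The Outcome assessments section confirms that EQ-5D is available at both ends of follow-up: "At the final 3-month follow-up, the three quality of life questionnaires will be repeated".

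**The concern.** A cost-effectiveness analysis answers a joint question: what is gained for what is spent. Two separate between-arm comparisons answer two different questions and leave the joint one open. The stated method therefore does not produce the outcome it is listed under.

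This matters because part of the trial's rationale is economic. The strengths and limitations list says of chlorhexidine that "this is a far cheaper, easy to formulate medication", and the sample size section raises the possibility that it is the most cost-effective option. If the row is followed as it stands, the trial report could carry a cost-effectiveness heading with nothing beneath it that supports or refutes that possibility.

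**Working it through.** **1. Is there a figure to reproduce?** No. The sample size section covers BSCVA only. For cost or EQ-5D the article gives no SD, power, correlation or willingness-to-pay threshold.

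**2. What the named outcome needs, against what the row supplies.** For a threshold λ, with ΔE the difference in mean effect and ΔC the difference in mean cost (chlorhexidine minus natamycin):

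- INB(λ) = λ·ΔE − ΔC
- Var(INB) = λ²·Var(ΔE) + Var(ΔC) − 2λ·Cov(ΔE, ΔC)

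The two comparisons can supply ΔE, ΔC and their two variances. They do not supply λ or the covariance. A reader given both mean differences could form a point value at a threshold of their own choosing, but could not attach an interval to it. The stated emphasis on a significance test does not promise even the two differences.

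**3. Does separating the two hide an advantage?** This can only be illustrated.

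Inputs from the article: 500 recruited, 15% drop-out, 1:1 allocation. So n = 500 × 0.85 / 2 = 212.5 per arm, and the standard error of a standardised mean difference is √(2/212.5) = 0.0970.

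Assumptions, not in the article: two-sided 5% tests, normal approximation, cost-effect correlation ρ from −0.3 to 0.3, and relative weight k = λ·SD(EQ-5D)/SD(cost) from 0.5 to 2. With each z positive when it favours chlorhexidine:

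z(INB) = (z_cost + k·z_effect) / √(1 + k² − 2ρk)

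*Case A, both components favourable.*

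- Suppose both observed z values are 1.5 (two-sided p = 0.13, neither significant).
  - Lowest (ρ = −0.3, k = 0.5): (1.5 + 0.75)/√1.55 = 1.81, probability of positive net benefit 0.965.
  - Highest (ρ = 0.3, k = 1): 3.0/√1.4 = 2.54, probability 0.994.
- Suppose instead true effects of 0.15 SD on each.
  - Each separate test has expected z = 0.15/0.0970 = 1.55 and power 34%.
  - Net benefit has power 46% to 74%.
  - In 200,000 simulated pairs, net benefit was significant while neither test was in 4% to 19%.

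*Case B, cost saving of 0.25 SD and no EQ-5D difference.*

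- Cost test: z = 0.25/0.0970 = 2.58, power 73%.
- Net benefit, lowest (ρ = −0.3, k = 2): 2.58/√6.2 = 1.03, power 18%.
- Net benefit, highest (ρ = 0.3, k = 0.5): 2.58/√0.95 = 2.64, power 75%.

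Case A favours the joint analysis. Case B mostly favours the plain cost comparison, and it is closer to what a non-inferiority trial of a cheaper drug expects.

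**4. Which costs count.** The row compares costs borne by patients. The article does not say who pays for the trial drops. If they are supplied free (an assumption), the difference in drug price does not enter the comparison at all.

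**The case against.** The best defence is that this is a condensed article. Mean cost and mean EQ-5D change by arm are the two inputs to any incremental analysis, and the ratio, threshold range and bootstrap are details often left to an analysis plan or economic plan that is not shown. A fuller plan may well exist. But the row does not defer its method. It states one, in the table given over to analysis details, and that method does not yield the outcome in the row's title. The text needs changing whatever else exists.

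A reader might go further and infer that two non-significant tests will be reported as no economic difference, so that a clear advantage is hidden. The documents do not support this. Nothing in them says the results will be read that way, and the perforation row of Table 4 shows the authors know that non-significance is not evidence of no difference. Nor is the numerical case strong. Two results at p = 0.10 do give 95% probability of positive net benefit when one component dominates, but that only restates a two-sided p value as one-sided. The 99% obtained by combining them (z = 2 × 1.645/√2 = 2.33) needs independence and equal weights. At ρ = −0.3 and k = 0.5 it is 1.5 × 1.645/√1.55 = 1.98, or 0.976. Case B shows that combining can also obscure a saving.

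It also stands that the consequence is limited. Cost-effectiveness is absent from the Objectives section and from the abstract's list of secondary outcomes, and is item 10 of 11 in Table 5.

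**Conclusion.** The point holds as a mismatch between a named outcome and its stated analysis. Followed as written, the plan gives no cost-effectiveness estimate and no joint uncertainty. This rests on the text alone and needs no assumption.

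The direction and size of any practical effect are undetermined. They depend on effect sizes, correlation, threshold and SDs that the documents do not give, and the illustrative ranges point both ways. The claim that the plan will conceal an advantage for chlorhexidine should not be made. This is a minor point on one secondary outcome. The non-inferiority conclusion on BSCVA is untouched.

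**What to change.** Rewrite the Table 4 row, and the matching analysis plan text, so that it states:

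1. The between-arm difference in mean direct patient cost, and in baseline-adjusted EQ-5D utility or 3-month QALYs, each with a confidence interval. Name the value set. With two measurements and linear change assumed, QALYs per patient are 0.25 × (baseline + 3-month utility)/2, so an adjusted utility difference at 3 months counts with weight 0.125.
2. Their combination as incremental net benefit over a stated threshold range, or as an incremental ratio. Use a bootstrap that resamples each patient's cost and effect together. Net benefit behaves better here, since a ratio is unstable when the effect difference is near zero.
3. A patient-perspective label, with a list of the costs collected. Either drop the statement that costs come from the EQ-5D or explain it.
4. The separate cost difference kept in the report, as it may be the more precise result if effects are similar.

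If the sponsor does not want this, rename the outcome as separate cost and EQ-5D comparisons and draw no cost-effectiveness conclusion.

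No new data collection is needed. The real cost is choosing and justifying a threshold range and a value set, which takes some care because the Trial setting section puts about half of outpatients as Indian nationals.

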#### Interim analysis

An interim analysis will be conducted for the DSMB by an independent statistician after 1/3 of patients recruited have completed follow-up.

### Patient and public involvement

Mixed methods descriptive cross-sectional studies with semistructured interviews and focus group discussions with patients and eye health providers were carried out in Sagarmatha zone, Eastern Nepal at various points in 2018.^33^ These conversations highlighted the delayed presentation often seen with FK combined with the often prohibitively high costs of treatment. Furthermore, treatment is not always felt to be effective. Eye health workers were keen to receive further training and highlighted the need for greater government support in the provision of eye care services in the community.

## Ethics and dissemination

Ethics committee and regulatory review and approval has been obtained from the Nepal Health Research Council (NHRC) Ethics Committee, Kathmandu, Nepal; the Department of Drug Administration (DDA), Kathmandu, Nepal; and the London School of Hygiene and Tropical Medicine Ethics Committee, UK. The trial is registered with the ISRCTN clinical trials registry. Protocol modifications are submitted to the relevant parties for review and/or approval. Table 5 summarises the study protocol and trial registration information. At the end of the study period, patients who still require treatment or follow-up will continue to be treated at SCEH as per routine clinical practice. The trial sponsor is the LSHTM. The results of this trial will be presented at local and international meetings and submitted to peer-reviewed journals for publication.

**Table 5 T5:** Registration data and protocol summary

Data category	Information
Primary registry and trial identifying no	ISRCTN Registry; ISRCTN14332621
Date of registration in primary registry	15 May 2019
Secondary identifying numbers	
Source(s) of monetary or material support	Wellcome Trust
Primary sponsor	London School of Hygiene and Tropical Medicine
Secondary sponsor(s)	
Contact for queries	[name] FRCOphth ([contact])
Title	Chlorhexidine 0.2% vs Natamycin 5% for the treatment of fungal corneal infections
Countries of recruitment	Nepal
Health condition(s) or problem(s) studied	Fungal keratitis
Intervention(s)	Participants will be randomised to either topical chlorhexidine 0.2% or topical natamycin 5%
Key eligibility criteria	1. Acute MK characterised by:
	Corneal epithelial ulceration >1 mm diameter
	Corneal stromal infiltrate
	Acute inflammation: for example, conjunctival injection, anterior chamber inflammatory cells, hypopyon
	2. Filamentous fungal hyphae visualised on smear microscopy and/or in vivo confocal microscopy
	3. Agree to be randomised to either treatment arm and able to give informed consent
	4. Agree to be followed up at 2 days, 1 week, 2 weeks, 3 weeks, 2 months and 3 months
	5. Adults (18 years and older)
Study type	Randomised controlled trial
Date of first enrolment	1 June 2019
Target sample size	500
Recruitment status	Recruiting
Primary outcome(s)	Best Spectacle Corrected Visual Acuity at 3 months by a trial certified optometrist
Key secondary outcomes	1. Time to full epithelial healing (slit lamp examination by ophthalmic clinician)
	2. Pin-hole visual acuity in logMAR at 3 months, trial-certified optometrist
	3. Scar/infiltrate size at 1 week, 3 weeks and 3 months (slit-lamp examination by ophthalmic clinician)
	4. Ulcer depth at 1 week and 3 weeks (slit-lamp examination by ophthalmic clinician).
	5. Hypopyon height at 1 and 3 weeks, (slit-lamp examination by ophthalmic clinician).
	6. Perforation and/or TPK by 3 months (slit-lamp examination by ophthalmic clinician).
	7. Positive culture rate at 1 week
	8. Ocular adverse effects at each follow-up visit (day 2, day 7, day 14, 3 weeks, 2 months, 3 months), slit-lamp examination by ophthalmic clinician
	9. Quality of life (QoL) assessed using: EQ-5D, WHO/PBD-VF20, WHOQOL-BREF (comparison between baseline and QoL measures at 3 months)
	10. Cost-effectiveness analysis, using EQ-5D data from 3 months and direct cost data
	11. Drug adherence at each follow-up visit (day 2, day 7, day 14, 3 weeks, 2 months, 3 months) while the patient is using study medications

EQ-5D, EuroQol-5 Dimension; LMIC, low-income and middle-income countries; MK, microbial keratitis; TPK, therapeutic penetrating keratoplasty.
